### Participant recruitment

2.2

Participants will be recruited from the Nagasaki University Hospital, where the subsequent study will also be conducted. The treating clinical research coordinator (CRC) will explain the study to the recruited individuals, and an informed consent form will be signed by those who agree to participate. This is a randomized crossover study, and will comprise 2 groups of patients. Both groups will be tested during the daytime nap, and the NHF device will be used concomitantly in 1 group.

After obtaining consent, subjects who meet the registration requirements will be randomly assigned to either of the 2 groups. Fifty-percent of the patients will be randomly assigned to each group for this crossover study as shown in the figure below.

Fifteen patients with stable COPD, aged 40 years or older, who need oxygen therapy and show FEV_1_% of <70% will be recruited from the Nagasaki University Hospital Respiratory Rehabilitation Center. Patients with hypercapnia due to COPD (arterial blood carbon dioxide partial pressure [PaCO2 ≧ 45 Torr]) in the stable period, history of exacerbation of COPD (moderate or higher) in the past year, and those requiring home oxygen therapy will also be recruited. Patients with hypercapnia due to COPD (arterial blood carbon dioxide partial pressure [PaCO2 ≧ 45 Torr]) in the stable period, history of exacerbation of COPD (moderate or higher) in the past year, and those requiring home oxygen therapy will also be recruited.

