#### Measurement of the index of kyphosis

2.5.6

Curvature of the spine from the 7th cervical vertebra to the 4th lumbar spinous process will be considered for quantitative evaluation of kyphosis using an 80 cm long flexible curved ruler (made by Shinwa) in an easy sitting position with no plantar contact. The shape will be traced on the paper as a straight line L (cm) connecting the seventh cervical and the fourth lumbar spinous processes of the curve. The distance from the straight line L to the apex of the curve will be H (cm), based on the formula by Milne et al.^[14]^ The ratio will be calculated as the index of kyphosis.

We will administer NHF (30–40 L/min of air and 5 L of oxygen [FiO_2_ = 0.3]) during nap sleep, in order to assess the immediate effect of the therapy on swallowing function in patients with COPD. Assess swallowing function. On the first measurement day, patients will be randomly allocated to either the high-flow nasal cannula oxygen therapy group or the no NHF therapy group with only oxygen (3 L oxygen [FiO_2_ = 0.3]) group (1:1). The second crossover measurement will be performed at least 1 week after the first with reversal of treatments in the 2 groups. In both groups, oxygen will be administered by a nasal cannula at a flow rate sufficient to cause an increase in PaO_2_ to over 60 mm Hg (oxygen saturation >90%, usually ≤3 L/min at rest). Patients with hypercapnia due to COPD (arterial blood carbon dioxide partial pressure [PaCO2 ≧ 45 Torr]) in the stable period, history of exacerbation of COPD (moderate or higher) in the past year, and those requiring home oxygen therapy (COPD GOLD stages 2 and 3) will be the target cases.

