### Adverse events

2.6

In this study, the NHF device will be secured onto the patient via a nasal cannula, and this could lead to discomfort. Moreover, an electrode for measurement of transcutaneous CO_2_ concentration will be attached to the anterior chest in both the NHF and non-NHF groups. This might cause temporary redness in patients with sensitive skin. Care will be taken to prevent undue harm to the patients in case of such adverse events.

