### Safety

2.9

The proposed safety evaluation indices of this clinical trial are as follows: adverse events are any undesired or unintended signs (including abnormal laboratory values, abnormal vital signs), symptoms, or illnesses that occur between the onset of use of the NHF device and the end of the last observation. The causal relationship between use of the device and occurrence of adverse events will not be of significance to the study. Pre-existing symptoms and diseases will be treated as complications and not adverse events. However, if the complications worsen after use of the NHF device, they will be treated as adverse events, and the day of confirmation of the deterioration will be the date of occurrence of the adverse event.

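### The adverse-event window opens at first NHF use, so in this crossover about half of the oxygen-only sessions, and the week or more after each, fall outside it while every NHF session falls inside

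*Protocol article*

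**What the plan says.** Section 2.9 (Safety) defines adverse events as undesired signs, symptoms or illnesses "that occur between the onset of use of the NHF device and the end of the last observation". The rule for pre-existing conditions has the same anchor: "if the complications worsen after use of the NHF device, they will be treated as adverse events". The section also states: "The causal relationship between use of the device and occurrence of adverse events will not be of significance to the study".

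The design is a randomized crossover. Section 2.2 gives the size: "Fifteen patients with stable COPD, aged 40 years or older", with half allocated to each group. Section 2.5.6 sets the order: "On the first measurement day, patients will be randomly allocated to either the high-flow nasal cannula oxygen therapy group" or to oxygen only, 1:1. It continues: "The second crossover measurement will be performed at least 1 week after the first with reversal of treatments in the 2 groups". Section 2.5 puts each measurement in a nap of 90 to 180 minutes.

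Section 2.6 (Adverse events) says the transcutaneous CO2 electrode is worn "in both the NHF and non-NHF groups" and adds: "This might cause temporary redness in patients with sensitive skin".

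The article gives no other start point for adverse-event recording.

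**The concern.** A window that opens at first use of the device suits a single-period study in which every participant receives the device at the outset. Here the opening date depends on the randomized order. For a patient who starts on oxygen alone, the control session and the interval after it come before the window. For a patient who starts on NHF, everything is inside it. A patient who withdraws after an oxygen-only first session never uses NHF and so has no window at all.

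The start point also sits badly with the rest of the text. Section 2.6 expects electrode redness under both conditions and treats it as an adverse event, yet under 2.9 the same redness in an oxygen-only session held first would not count. Section 2.9 sets causality aside, so the NHF anchor cannot be explained as a way of restricting capture to device-related events.

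At stake is the safety record. Electrode redness, an exacerbation, or worsening hypercapnia in a hypercapnic patient would go unclassified if it arose in an oxygen-only first session or in the interval after it. Sections 2.2 and 2.5.6 name hypercapnic patients as candidates, without giving their share. Any listing by condition would be tilted against NHF at equal true rates, in a study whose purpose is to inform a later verification study.

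**Working it through.** The plan gives no figure on this point, so there is none to reproduce. The sessions can be counted from the design.

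**Inputs**
- Patients: 15 (section 2.2).
- Allocation to order: 1:1 (sections 2.2 and 2.5.6), so 7 or 8 patients have oxygen only first.
- Session length: 90 to 180 minutes, i.e. 1.5 to 3 hours (section 2.5).
- Interval between sessions: at least 7 days (section 2.5.6).
- Assumption: all patients complete both sessions.

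**Coverage by order**

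| Order | First session | Interval | Second session |
|---|---|---|---|
| NHF, then oxygen only | inside | inside | inside |
| Oxygen only, then NHF | outside | outside | inside |

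**Share of sessions outside the window** = oxygen-first patients / 15
- Oxygen only: 7/15 = 47% or 8/15 = 53%.
- NHF: 0/15 = 0%.

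**Oxygen-only session time outside the window**
- Lowest: 7 × 1.5 h = 10.5 h.
- Highest: 8 × 3 h = 24 h.

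**Interval time, at the one-week minimum**
- After an oxygen-only first session: 7 × 7 = 49 to 8 × 7 = 56 patient-days, none covered.
- After an NHF first session: 8 × 7 = 56 to 7 × 7 = 49 patient-days, all covered.

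**Apparent excess under NHF.** Assume the same true event rate *p* per session in both conditions. Events captured are 15*p* under NHF and (15 − oxygen-first patients) × *p* under oxygen only. The rate cancels:
- 7 oxygen-first: 15/8 = 1.9.
- 8 oxygen-first: 15/7 = 2.1.

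**Sensitivity to imbalance.** Section 2.5 uses COPD stage as an allocation factor, so the split could be slightly uneven. If 6 to 9 patients were oxygen-first (an assumption), the share outside would be 6/15 = 40% to 9/15 = 60%, and the ratio 15/9 = 1.7 to 15/6 = 2.5. The direction does not change.

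**After the change.** With the window opening at the first session in either order, 15 of 15 NHF sessions, 15 of 15 oxygen-only sessions and all 15 intervals are covered.

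**The case against.** The strongest reply is that 2.9 is loosely worded and little depends on it.

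- **Convention.** Starting the window at first use of an investigational device is common. That holds for single-period studies; it does not make the rule suit a crossover.
- **Causality.** Disregarding causality decides which events count once the window is open, not when it opens, so the two rules are compatible. This is right as logic. The causality sentence only removes one possible justification for the NHF anchor. The real tension is with 2.6.
- **Section 2.6 as evidence of intent.** It suggests that staff will attend to events in both conditions. That is plausible, but the same anchor appears in two sentences of 2.9, and no other definition is given.
- **In-session hypercapnia.** TcPCO2, SpO2 and respiratory rate are secondary endpoints measured in both conditions. A deterioration during an oxygen-only nap would be in the data, and only its classification as an adverse event would be lost. This stands. It does not extend to the interval, for which no such measurement is described.
- **Size.** Section 2.11 plans no formal comparison of adverse events, so the 1.9–2.1 ratio applies only if events are listed by condition. The uncovered interval follows one nap on low-flow oxygen in patients who already need oxygen, and much of what happens then would be background disease. The expected effects are mild, and the article gives no withdrawal rate.

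These points limit the weight of the concern. None of them makes the start point right for this design.

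**Conclusion.** The concern holds. Followed as written, section 2.9 leaves 7 or 8 of the 15 oxygen-only sessions, and at least 49 to 56 patient-days of interval, outside adverse-event capture, and no NHF session. This rests on 15 completing patients and a near-even split. The 1.9–2.1 ratio further assumes equal true event rates per session and a listing by condition. Each withdrawal between an oxygen-only first session and the second visit would add a patient with no window.

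The harm is confined to incomplete and unbalanced safety data in a small exploratory trial; the endpoints in 2.7 and 2.8 are untouched. The point is a stated rule that does not fit the crossover, not detail left to a fuller document. The change is worth making, but the trial's efficacy conclusions do not depend on it.

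**What to change.** In section 2.9, open the adverse-event window at the start of the first measurement session, whichever condition comes first, and close it at the end of the last observation as now. Use the same start point in the sentence on worsening of pre-existing conditions. Assign each event to the first session, the interval or the second session, together with the condition most recently received. Keep patients who withdraw before any NHF use in the safety listing.

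The cost is two phrases and one attribution rule. No new procedure is needed; the extra work is adverse-event recording for 7 or 8 sessions and the intervals after them. The endpoints in 2.7 and 2.8 stay as they are.

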### Data collection and management

2.10

The assignment and input tables to be used in this study will be created with the Research Electronic Data Capture (REDCap) software. The study will be conducted after the registered patients are allocated to groups and the data collected from the medical records are submitted to the researcher. A physician, co-doctor, and coworker will assign an ID to the medical records of each patient, which will be provided to the researcher. The Principal Investigator or Co-Researcher will approve the observation/inspection/evaluation data of each research subject immediately after confirming the content. The Principal Investigator and the Clinical Research Center Data Management staff will perform a visual and logical check of the data entered in the case report. The Principal Investigator or the Research Coordinator will be contacted in case of any discrepancies or queries regarding the data. The case will be fixed by performing data lock after resolving the issues and modifying the data (if indicated). The data management staff will be responsible for overseeing the process of correction of errors that arise after a case is locked. Proper conduct of the study will be monitored in accordance with the research plan.

### Statistical analyses

2.11

Considering the exploratory nature of this study, we will estimate the incidence rate for each study parameter and use the information to calculate the necessary sample size for the verification study, in order to achieve statistical significance.

Specifically, the rate of appearance of the expiratory phase after swallowing of saliva and the frequency of swallowing during the measurement period in the NHF device and control groups will be calculated. The difference (ratio) between the 2 groups and the 95% confidence interval on both sides will be calculated. For other items, the average value and standard deviation for each group will be calculated manually.

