**Figure 2 F2:**
[figure not shown]
After obtaining informed consent, subjects who meet the registration requirements will be randomly assigned to either of the 2 groups. Fifty-percent of the patients will be randomly assigned to each group for this crossover study. The experimental group will be Oxygen therapy group with NHF application (40 L/m with air + 5 L O_2_ FiO_2_ = 0.3), control group will be Oxygen therapy group with nasal cannula (3 L/m oxygen FiO_2_ = 0.3).

The primary endpoint will be the occurrence rate of the expiratory phase after swallowing of saliva.

The Clinical Research Review Board of Nagasaki University has approved the study protocol. The study will be conducted at Nagasaki University Hospital in Japan. The study is registered in the jRCTs. The study will be conducted in accordance with the principles of the Declaration of Helsinki and the established best clinical practices of Japan. This is an exploratory study aimed at collecting information for conducting a verification study. Therefore, the number of cases will be set based on the feasibility in our hospital.

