### Outcome

2.7

The primary endpoint will be the frequency of swallowing of saliva during the measurement period and the rate of appearance of the expiratory phase.

The secondary endpoints will be: time-weighted average value of TcPO_2_ (average partial pressure during the observation period), time-weighted average value of TcPCO_2_ (average partial pressure during the observation period), time-weighted average value of SpO_2_ (average oxygen saturation during the observation period), time-weighted average respiratory rate (average respiratory rate during the observation period).

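### Section 2.11 words the analysis of a two-period crossover as a comparison of two groups, which drops the within-patient pairing from the 95% interval and from the summaries meant for planning the next study

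*Protocol article*

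**What the plan says.** The design is clear. Section 2.2 states: "This is a randomized crossover study, and will comprise 2 groups of patients". Allocation is 1:1 ("Fifty-percent of the patients will be randomly assigned to each group for this crossover study"), and section 2.5.6 has every patient measured under both conditions: "The second crossover measurement will be performed at least 1 week after the first with reversal of treatments in the 2 groups". Recruitment is fixed at 15 ("Fifteen patients with stable COPD, aged 40 years or older, who need oxygen therapy"), and the text following Figure 2 in section 2.1 gives the basis: "Therefore, the number of cases will be set based on the feasibility in our hospital".

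The primary endpoint in section 2.7 has two parts: "The primary endpoint will be the frequency of swallowing of saliva during the measurement period and the rate of appearance of the expiratory phase". Both come from repeated swallows within one nap of one patient.

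Section 2.11 then has these two quantities calculated in the NHF and control groups and adds: "The difference (ratio) between the 2 groups and the 95% confidence interval on both sides will be calculated". For every other item, "the average value and standard deviation for each group will be calculated manually". The same section says that the results will be used to size a later verification study. It mentions no within-patient difference, period or unit of analysis.

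**The concern.** In sections 2.2 and 2.5.6 a group is a set of patients defined by the order of treatment. In section 2.11 the same word means a treatment condition, and the contrast is written as it would be for two separate sets of people. The discussion part of the abstract does likewise when it sets a device group against a control group that did not use the device. The section goes beyond leaving a formula open: it names a contrast and a form of summary, and neither matches the design.

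Two things are at stake. The first is the primary 95% interval, the main inferential output of the study. An analyst who takes section 2.11 literally would either compare two sets of patient rates as independent, or compare two overall proportions of swallows. Neither uses the fact that each patient serves as their own control. The second is planning. The study is meant to inform the size of a verification study, and a mean and SD per condition do not show how far a patient's two measurements agree.

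**Working it through.** **What there is to reproduce.** Nothing numerical. The number of patients rests on feasibility, and the article gives no effect size, SD, expected rate or swallow count. From the document I take 15 patients, two conditions per patient, 1:1 allocation to order and a two-sided 95% interval. All else below is assumed.

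**1. Patient-level rates, unpaired against paired.** Let s be the SD of patient rates in each condition and ρ the within-patient correlation.

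- Unpaired half-width: t(28) · s · √(2/15), with t(28) = 2.048.
- Paired half-width: t(14) · s · √(2(1 − ρ)/15), with t(14) = 2.145.
- Ratio: (2.048/2.145)/√(1 − ρ) = 0.955/√(1 − ρ).

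| ρ (assumed) | √(1 − ρ) | unpaired/paired width |
|---|---|---|
| 0.3 | 0.837 | 1.14 |
| 0.5 | 0.707 | 1.35 |
| 0.7 | 0.548 | 1.74 |
| 0.8 | 0.447 | 2.14 |

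At ρ = 0 the ratio is 0.955, so the loss appears only when a patient's two naps are positively correlated, which is the usual reason for choosing a crossover.

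**2. Swallows pooled by condition.** This was checked by simulation with no true effect and 20,000 trials per scenario. Assumptions: typical expiratory rate about 70% (logit 0.85), a mean of 30 swallows per nap varying between patients, and a between-patient SD of 1.0 on the logit scale. The patient-by-condition SD was varied. Each cell shows coverage of the nominal 95% interval and its mean full width.

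| patient-by-condition SD | pooled swallows | unpaired patient rates | paired |
|---|---|---|---|
| 0 | 95.0%, 0.123 | 100.0%, 0.312 | 95.4%, 0.143 |
| 0.3 | 88.1%, 0.123 | 99.9%, 0.321 | 95.2%, 0.168 |
| 0.5 | 78.5%, 0.123 | 99.8%, 0.336 | 94.9%, 0.203 |
| 0.8 | 64.7%, 0.124 | 99.3%, 0.366 | 95.1%, 0.264 |

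The pooled result is sensitive to swallow counts. At SD 0.5 it covers 88.7% with 10 swallows per nap and 67.6% with 60. It also depends on how counts vary. With 30 swallows, further runs of the same setting gave:

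- SD 0: 96.6% with fixed counts, 82% when counts vary independently from nap to nap.
- SD 0.5: 83% with fixed counts, about 70% when counts vary independently from nap to nap.

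The pooled interval can therefore be about right, slightly conservative or clearly too narrow. The paired interval stays near 95% in every scenario of the table.

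**3. Period.** Fifteen patients split at best 8 to 7 between orders. If period 2 differs from period 1 by π, the unadjusted mean of the within-patient differences carries (8π − 7π)/15 = π/15 of it in absolute size. This bias is small, but the period effect also enters the SD of the differences. Adjustment removes both.

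**4. Planning the next study.** The SD of the paired differences is s√(2(1 − ρ)), and ρ cannot be recovered from two per-condition SDs. As an illustration, assume a 10-point difference, s = 0.15, 80% power and two-sided 5%:

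- (s(1.960 + 0.842)/0.10)² = (4.203)² = 17.66.
- Parallel design: 2 × 17.66 = 35.3, so 36 per group and 72 in total.
- Paired design, 2(1 − ρ) × 17.66: 25, 18 or 11 patients at ρ = 0.3, 0.5 or 0.7.

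Per-group summaries cannot tell the last three apart.

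**The case against.** The strongest reply is that the article uses the word group loosely throughout, including in sentences that plainly describe a crossover, so its use in section 2.11 is weak evidence of an independent-samples analysis. No interval method, pooling rule or unit of analysis is given. The text would also fit one rate per patient compared within patients, and the full protocol or analysis plan may say so. The absence of a formula, a period term or a clustering adjustment from a condensed article is no fault in itself.

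Much of this stands. A reader might infer that swallows will be pooled, or that the interval is bound to be wrong. The document supports neither: pooling is neither stated nor excluded, and some settings above show no undercoverage at all. The coverage figures rest on variances and swallow counts that the article does not give.

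Two further inferences also go too far. One is that false-positive findings will follow. The study is exploratory, sized on feasibility, and states no hypothesis test. The other is that the next study will certainly be mis-sized. The article never says that the verification study will be a crossover, and for a parallel-group study the per-group rates and SDs would be the relevant inputs.

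What remains is that section 2.11 does more than stay silent. It specifies a contrast between two groups, and for the other items a summary by group only. As worded, neither fits a design in which each patient is measured twice.

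**Conclusion.** The concern holds as a mismatch between the stated analysis and the stated design. If section 2.11 is followed as an independent-group comparison, the primary interval is miscalibrated:

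- Comparing patient rates unpaired gives an interval about 1.35 times the paired width at an assumed within-patient correlation of 0.5, and 1.74 times at 0.7.
- Pooling swallows may give too narrow an interval. With 30 swallows per nap, coverage was roughly 70% to 83% at a patient-by-condition SD of 0.5, and 82% to 97% with no such variation. These figures indicate direction and scale only.

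For the secondary endpoints, the planned summaries omit both the treatment contrast and the SD of paired differences, whatever interval method is chosen for the primary endpoint. That SD matters for planning if the verification study is a crossover. The consequence is misstated precision and a possible mis-sizing of the next study, without any inflation of a confirmatory error rate. Both conditions are recorded for each patient, so a correct analysis needs no change to the design or data collection.

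**What to change.** Reword section 2.11 as follows:

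- For each patient, compute the expiratory-phase rate and the swallow frequency under NHF and under control.
- Estimate the mean within-patient difference (or ratio) with a two-sided 95% interval adjusted for period, with the patient as the unit of analysis.
- Give the same paired contrast and interval for the four secondary endpoints.
- Report the SD of the paired differences beside the per-condition SDs, so that the verification study can be sized under either design.
- Call the treatments conditions and the orders sequences, so that one word no longer serves for both.

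The cost is a few sentences and a little more analysis work. The period adjustment uses one degree of freedom (13 instead of 14). The interval may be wider than one from pooled swallows.
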